## Abstract

**Background:**

Grief has been associated with several long-term negative outcomes for both surviving parents and bereaved children, especially when it is preceded by unnatural and violent deaths. Nevertheless, it has been an underestimated public health problem with few, if any, empirically documented early preventive intervention programs. The best time to start them is also a major question that requires further evidence.

**Objective:**

The overall aim of this study is to assess the feasibility of a future larger trial, informing sample size calculation, recruitment/randomization procedures, retention rates, data collection forms, and outcomes. This study will also explore: (1) the early effects of Systematic Early Intervention for Bereaved (SEIB) compared with the early effects of care as usual, and (2) the effects of the immediate SEIB version compared with the effects of the delayed SEIB version.

**Methods:**

In a pilot randomized controlled trial (RCT) with a delayed intervention design, suddenly bereaved families will be assigned to: the immediate-SEIB intervention group, or the delayed-SEIB intervention group. Participants will fill in a set of self-report measures at baseline, and after 3, 6, and 9 months follow-up. Quantitative data on traumatic stress symptoms, complicated grief, psychological wellbeing, daily functioning, social support, parental capacity, parenting practices, and family functioning will be collected to inform power calculations and explore SEIB’s preliminary effects. Data on the flow of participants throughout the trial will be analyzed in order to estimate recruitment and retention rates. Two brief questionnaires were developed to assess recruitment procedures, randomization, and data collection materials.

**Results:**

Recruitment for this project started in August 2015, and follow-up data collection will be completed in June 2017.

**Conclusions:**

This study prepares the ground work for the design and implementation of a main trial and may add preliminary knowledge to the significance of early supportive practices that have been commonly used regardless of their sparse evidence.

## Introduction

Bereavement is a natural and common event, and most people are generally able to adapt to the resulting grief over time and regain function in their everyday life [1]. However, approximately 10% to 22% of bereaved people experience deleterious forms of mental distress that result in mental health deterioration [2]. The loss of a significantly loved person through death can be a complex and disturbing life event that is linked to greater psychological problems, physical illness, and mortality. Individual grief reactions can vary from minor and shorter responses to more severe and prolonged manifestations [3]. More importantly, unnatural and violent deaths significantly cause more severe after effects than natural deaths [4].

Complicated grief encloses the more severe and prolonged symptoms that hamper social and occupational functioning [3,5]. It has been found to be related to higher rates of mental disorders, sleep problems, suicidality, cardiovascular and cancer diseases, and lack of social support [6-10]. Preoccupied thoughts of the deceased, intense searching and yearning for the deceased, avoiding memories of the deceased, death denying, and crying are among the core symptomatology of complicated grief [11]. In addition, other comorbid symptoms that meet the criteria for depression and/or posttraumatic stress disorder (PTSD) have been documented [12].

Acknowledging the individual and contextual risk factors for the potentially chronic complicated grief outcomes increase awareness on the subset of bereaved people who are in major need of assistance [13]. In several studies, the death of a parent is emphasized as one of the most demanding and traumatic events that can be experienced in childhood and youth [14,15]. It has been found to enhance the risk for a wide range of mental and behavioral problems, even when controlling for previous risk factors [16]. Parentally bereaved children have shown clinically significant indicators of psychological distress (eg, depression, anxiety, somatic complaints, withdrawal), traumatic grief (eg, yearning for the deceased, diminished acceptance of the death), lower academic functioning and self-esteem/self-efficacy, higher external locus of control, and social problems [17-19]. Furthermore, parentally bereaved children who suddenly and unexpectedly lose a parent (eg, following a suicide, an accident, or a natural death) were at greater risk of developing depression and PTSD symptoms [20]. A sudden and unexpected loss is seen as an existential crisis that threatens self-beliefs about safety [21] and self-ability to accept, confront, and adapt to what has occurred [22].

The manifold negative effects of parental death in childhood seem to be linked to increased rates of disorder in both bereaved parents and their children [20,23]. The surviving parents have to raise their children under extremely difficult conditions. On the one hand, they must deal with the loss of their partner and their own psychological problems, while facing the pressure of being a single parent [24]. On the other hand, parentally bereaved children can pose additional challenges for parents, expressing their adjustment problems through more disruptive behaviors [25].

In view of these detrimental influences of bereavement-related psychological distress on both the individual and the family system, it is crucial to break this cascade of negative cycles. It highlights the need of developing effective interventions aimed to promote resilience for both bereaved parents and their children, especially in the early stages that follow death [26,27] where the disabling consequences have been more strongly noticed [3]. Several clinicians and researchers in the loss and trauma field have emphasized the usefulness of early crisis intervention [26-28]. They argue that early intervention favors the attenuation of the initial dysfunctional appraisals and enables a better case management, and maximizes the chances of a more adaptive developmental pathway [27]. Norwegian studies on the users’ perspectives show that traumatic bereaved participants ask for: (1) immediate assistance, (2) outreach help, (3) help for their children, (4) information about the event and potential reactions, (5) possibility to meet with others who experienced similar situations, and (6) help over time [22,29]. Nevertheless, meta-analytic findings failed to show a significant effect of preventive approaches, pinpointing diverse methodological limitations among the studies [30]. To our knowledge, none of these studies assesses interventions taking place immediately after the loss. The start of these preventive programs ranges from 2 to 6 months post loss [31,32]. Thus, it is essential to develop well-designed randomized controlled studies [33] attempting to increase understanding about the best time to provide early intervention.

In line with this, the Systematic Early Intervention for Bereaved (SEIB) was developed. It is the first Norwegian program that proposes professional family assistance starting in the first days after a sudden and traumatic loss. Within a family perspective, SEIB seeks to facilitate natural mourning, resolve grief complications, promote parental capacity, and help the bereaved partner and their children to develop or enhance satisfying relations/activities, and to regain control over their life. The basis of this approach is from the field of early crisis intervention [26-28]. The existing literature [3,25], the wishes for help as expressed by the bereaved themselves [22,29], and our extensive clinical practice, are at the heart of this approach.

The present study aims to expand knowledge in early intervention on family -related psychological distress following a sudden and unexpected death of a partner/parent. It consists of a pilot study to assess the feasibility of a future main trial, as well as SEIB’s preliminary impact with suddenly bereaved families. Accordingly, the specific aims are to:

1. Assess recruitment materials and procedures.

2. Assess the usefulness of randomization and data collection materials.

3. Obtain reliable estimates regarding recruitment and retention.

4. Provide information on power calculations and possible outcomes (both parents and children).

5. Explore the 3-month SEIB effects' on traumatic stress symptoms, complicated grief symptoms, psychological wellbeing, daily functioning, social support, parental capacity, parenting practices, and family functioning, compared with the 3-month effects of care as usual.

6. Explore the 3- and 6-month effects of the immediate-SEIB version on traumatic stress symptoms, complicated grief symptoms, psychological wellbeing, daily functioning, social support, parental capacity, parenting practices, and family functioning, compared with the 6- and 9-month effects of the delayed-SEIB version.

## Methods

### Trial Design

As outlined in Figure 1, this study is a one-center, pilot, randomized controlled trial (RCT) with a delayed intervention design in which suddenly bereaved families will be randomly assigned to: the immediate-SEIB intervention group (receiving SEIB in the aftermath of the loss) or the delayed-SEIB intervention group (control condition; receiving SEIB 3 months post loss). Both groups can make use of care as usual from their communities.

**Figure 1 figure1:**
[figure not shown]
Design of the study protocol.

### Participants and Eligibility Criteria

The sample will include bereaved families with children younger than 18 -years old, who suddenly and unexpectedly lose a partner and a parent. Bereaved partners and their children, aged from 12 - to 18 -years old, will be the informants of the study. To ensure a homogeneous sample, all family members must speak Norwegian. Eligible families are those who satisfy both of the criteria listed in Textbox 1.

Inclusion criteria.Criterion for unexpectedness: the loss shall occur following an accident, a suicide, a murder, or a disease, as well as situations where people are missing (presumed dead).Criterion for suddenness: the loss shall occur shortly, or within the same day as the event/disease happened or started. This period can be extended up to 5 days for people who do not regain consciousness after the incident (eg, illness/accident/suicide, etc). The families cannot enter this study later than 3 weeks after the death.

Potential participants with severe medical conditions for both bereaved partner and their children, such as serious physical impairment, intellectual deficit, severe child developmental problems, borderline personality disorder, history of psychosis (eg, schizophrenia, bipolar disorder), current substance use disorder (in the past 6 months), severe suicidal risk, or dementia will be excluded. Families receiving concurrent psychotherapeutic intervention for problems concerning loss and/or trauma will also be excluded.

### Recruitment and Randomization

A continuous recruitment will occur through referrals from crisis teams of the entire county of Hordaland in Norway. Health care units of the general hospitals in Hordaland, as for instance emergency and intensive care units, will also recruit for this study to secure the inclusion of those who lose a family member to acute disease.

Bereaved partners will be informed about the study the first time they are in contact with the health care personnel immediately after the death, and potential participants will be given a study information brochure. They will then receive a phone call to schedule an appointment for a first meeting at their homes (or at our center if they prefer so). At the end of this first meeting, the families will receive a sealed opaque envelope containing information regarding their random group allocation. Randomization will be previously performed by an external and independent research assistant who will use blocks of 6 families (3 allocated to each arm of the trial) [34]. For each block of 6, containing 3 intervention condition cards and 3 control condition cards, the researcher will randomly draw a card assigning it to one family according to its order of entrance in the study. This will help to randomly vary the order of interventions within each block. Due to the nature of the intervention, it will not be possible to blind participants to group assignment. However, the researchers who visit and phone the families have no previous knowledge concerning allocation until the end of the first meeting. In addition, they will not be involved in the intervention phase.

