### Sample Size and Statistical Analyzes

In light of the small state of knowledge about early intervention in the aftermath of a potential traumatic death of a partner/parent, this study is not aimed to test SEIB effectiveness. Power analysis is not used to determine the final sample size, because it is not recommended for pilot studies that do not rely on inferential statistical tests [57]. Following a general rule of thumb that suggests the inclusion of 30 participants or more to determine a parameter (eg, mean/standard deviation) of an outcome variable [58], we will recruit a total of 60 families (30 families in each group). Rather than focusing on hypothesis testing, this pilot study builds on the practical limitations of recruitment and topics of incertitude, such as the need to gather initial estimations for sample size calculation [57,59,60].

Statistical analyzes will be computed using IBM SPSS Statistics and multiple imputation methods will be used to impute values of missing data [61]. Descriptive data will be computed to characterize the sample. On the basis that pilot study analyzes should be mostly descriptive and should provide confidence interval estimation [60,62], descriptive statistics (including mean, percent, standard deviation, and range), and confidence intervals will be used to describe all outcome variables at T1, T2, T3, and T4 providing important information regarding recruitment and randomization procedures, data collection forms, retention rates, future power calculations, and SEIB most appropriate outcomes.

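### A single published block size of 6 means the stated allocation concealment is not guaranteed: up to 25% of allocations can be deduced by researchers who know the size and track the sequence

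*Protocol article*

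**What the plan says.** All of the allocation procedure is under Recruitment and Randomization in the protocol article. An external, independent research assistant prepares the sequence and is the one "who will use blocks of 6 families (3 allocated to each arm of the trial"). The mechanism is drawing cards: "For each block of 6, containing 3 intervention condition cards and 3 control condition cards", each card drawn "assigning it to one family according to its order of entrance in the study". Neither a second block size nor stratification is mentioned.

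On concealment, at the end of the first meeting "the families will receive a sealed opaque envelope containing information regarding their random group allocation". The same section concedes that "it will not be possible to blind participants to group assignment", but states that "the researchers who visit and phone the families have no previous knowledge concerning allocation until the end of the first meeting" and that these researchers take no part in delivering the intervention.

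Two other sections matter. Trial Design says that "this study is a one-center, pilot, randomized controlled trial (RCT) with a delayed intervention design". Sample Size and Statistical Analyzes says "we will recruit a total of 60 families (30 families in each group"). The Results section reports that enrolment was under way when the article appeared, so the block size became public during recruitment.

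**The concern.** A sealed opaque envelope hides its own contents. It does not hide what the earlier, opened envelopes imply about it. Once three families in a block of 3 + 3 have gone to one arm, every remaining family in that block must go to the other. With one centre and one list in order of entry, the sequence is easy to follow, and the visiting researchers are told each result when the meeting ends. The statement that they have no prior knowledge therefore depends on what they know and remember, and the design as described does not secure it.

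These researchers phone and meet families before the allocation is revealed. Someone who could foresee the arm might, without intending to, let it influence how quickly a visit is arranged within the three-week entry limit or how the study is presented. That could make the two groups differ at entry and so affect the between-group effect sizes the pilot will report. The pilot's second aim also covers the usefulness of the randomisation materials, so a predictable scheme could be carried into the main trial.

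**Working it through.** **Inputs, all from the protocol article.** Block size 6, ratio 3:3, order of entry (Recruitment and Randomization); 60 families, 30 per group (Sample Size and Statistical Analyzes); one centre (Trial Design).

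**The plan's own figure.** 60 / 6 = 10 complete blocks, and 10 × 3 = 30 families per arm. This matches the stated split.

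**Allocations that are certain from the earlier ones.** A 3 + 3 block has C(6,3) = 20 equally likely orders. An allocation is certain when one arm's three cards are already used.

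- Positions 1 to 3: never certain.
- Position 4: certain if the first three families all went to one arm. This is 2 of 20 orders = 10%.
- Position 5: certain if three of the first four went to one arm, so that the last two cards are alike. This is 2 × 4 = 8 of 20 orders = 40%.
- Position 6: always certain, 100%.

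Expected number per block: 0.1 + 0.4 + 1.0 = 1.5. The closed form 2m/(m + 1) with m = 3 agrees: 6/4 = 1.5. As a share this is 1.5 / 6 = 25%, and over 10 blocks it is 10 × 1.5 = 15 of 60 families. Ten of these are the last family of each block.

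**Range.** The 25% applies to an observer who knows the block size and has seen every earlier allocation in order. A researcher who has seen fewer than three of the earlier families in a block can be certain of nothing in it. The share of certain predictions therefore runs from 0% (block size unknown, or sequence not followed) to 25% (known and fully tracked).

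**Best guess.** Always guessing the arm with more cards left is right for m + (2^(2m)/C(2m,m) − 1)/2 families per block. With m = 3 this is 3 + (64/20 − 1)/2 = 3 + 1.1 = 4.1 of 6, or 68.3%, against 50% under simple randomisation.

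**Effect of varied block sizes.** The table shows 3,000 simulated trials of 60 families for each mixed set, with an observer who knows the set of possible sizes and all past allocations. The row for fixed 6 is exact.

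| Block sizes | Certain predictions | Best guess correct |
|---|---|---|
| Fixed 6 | 25.0% | 68.3% |
| 4, 6 | 5.6% | 69.1% |
| 4, 6, 8 | 2.2% | 67.8% |
| 2, 4, 6 | 4.1% | 70.0% |

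Varying the sizes removes most of the certainty. It leaves the guess rate almost unchanged, because every permuted block returns to balance whatever its length. A block of 2 is the most guessable on its own: the second family is always known, so the guess rate is (0.5 + 1) / 2 = 75%.

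**The case against.** The strongest reply is that 25% is a ceiling. To reach it, the people who phone and visit must know the block size, pool every earlier result in exact order of entry and know where each block begins. The article says none of this. It refers to researchers in the plural, so visits may be divided, and a full protocol may withhold the block size from field staff. This stands. A reader might infer that the visiting researchers do foresee a quarter of allocations; the document supports only that they could, under those conditions.

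A reader might also infer a specific route to bias: that these researchers apply the judgement-based exclusions, or help with the baseline questionnaires before the envelope is opened. The article does not say who applies the exclusions. It says a researcher is present at baseline, but does not state the order of questionnaires and envelope. Both routes are plausible but inferred.

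There are real safeguards: an external assistant, sealed opaque envelopes, late disclosure and separation of the visiting researchers from treatment. The outcomes are self-reported, and all families are offered the programme eventually, which weakens any motive to steer allocation. These points limit the likely harm. They do not prevent deduction from a fixed block, which needs only the block size and the past allocations.

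**Conclusion.** The point holds as a conditional one. With a single published block size of 6 in an open, one-centre trial, up to 25% of allocations (15 of 60) are deducible before the first meeting if the visiting researchers know the size and track all earlier results. The claim of no previous knowledge is therefore not guaranteed by the design. The figure is lower if results are not shared among them, and nothing in the article shows that any allocation was in fact predicted.

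The size and direction of any resulting bias are unknown, and the pilot is descriptive and does not test effectiveness. This is a worthwhile, inexpensive improvement and does not invalidate the study. The 68% best-guess rate should not be presented as a harm that varied blocks would cure, since it stays at about 68% after the change.

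**What to change.** For families not yet randomised, have the external assistant prepare a new sealed list with randomly varied block sizes, for example 4, 6 and 8. Leave out size 2. Withhold the sizes from the researchers who phone and visit, and keep them out of public text until enrolment ends. Amend the concealment sentence under Recruitment and Randomization to say that block sizes vary and are not disclosed to these researchers, and to claim no more than that secures.

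With sizes 4, 6 and 8, certain predictions fall from 25% to about 2%, even for an observer who knows the set of sizes. The best-guess rate stays at about 68%.

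The cost is one new list and a possible final imbalance of a few families between arms, because recruitment may stop partway through a block.

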### Intervention

SEIB is a multidimensional clinical- and theory-based program designed to strengthen the resources of parentally bereaved children and their parents while adjusting to the major changes of a sudden and unexpected death of a parent/partner [26,27]. As suggested by others [28,30,35], SEIB attends to the unique needs of each bereaved family member, mapping the new ground that the families are entering and stimulating the benefits of the social network support. It has been acknowledged that bereavement is a process that differs among individuals; hence, intervention programs should be tailored to each individual’s needs [30].

Through a minimum of 5 sessions (or more if deemed necessary), SEIB’s focus is placed on: (1) stabilizing the situation and decreasing arousal (eg, by emotion regulation) [26,27], (2) facilitating individual coping skills and healthy grief reactions [26-28], (3) promoting positive parenting (warmth, open communication, effective discipline) [25,26], (4) encouraging the adaptive expression of emotions among family members [25,26], (5) empowering parent-child relationship and family interactions [25], (6) stimulating occupational and social functioning [26], and (7) activating/monitoring social support provision [27,28].

#### Session 1

Session 1 is to take place within the first 3 days after the loss, whenever possible (no later than 3 weeks post loss). The initial aim of this session is to reduce bodily activation by calming and stabilizing family members, and stimulating their perception of being cared for. In addition, this session focuses on parental psychoeducational information about their children needs’, stimulating open and direct communication, and ensuring that facts are shared within the family. In order to contextualize the facts, to establish coherence/structure, and secure equal access to facts within the family, every family member is invited to narrate their loss experience (facts, not feelings) with a special emphasis on the importance of hearing the children’s perspective. Furthermore, this session provides concrete advice on sleep, work/school, use of medication, participation in rituals, and how to maximize support from their social network (for both children and adults). At the end of this session, the parents receive a booklet as a guide for them to talk with their children about death [36].

#### Session 2

Session 2 takes place within 2 to 4 weeks post loss. The initial aim of this session is sharing of factual information concerning the circumstances of the death and the death notification, as well as new available information (ie, from police, health personnel, or others), ensuring that everyone in the family (including children) have access to the information they need. As in the first session, this session continues to secure open and direct communication within the family. In addition, psychoeducational information concerning basic and common grief reactions is combined with concrete advice for dealing with school/work re -entry. Grief and traumatic reminders, guilty feelings, and intrusive material are also addressed, and self-help methods introduced. The use of self-help methods is based on feedback from the family members on what they find particularly difficult. Usual relevant self-help methods refer to techniques that help to gain control over intrusive memories, reduce bodily arousal or tension, and improve sleep hygiene [37]. Finally, this session discusses how family members interact with each other, and how they can effectively support and take care of each other. New distribution of roles among family members and how to make good use of their social support networks are addressed.

#### Session 3

Session 3 takes place within 5 to 7 weeks post loss. The initial aim of this session is to address and process trauma aspects of the loss. Family members go through what they knew and thought about what happened, as well as their sensory experiences and body reactions at the time (especially the most difficult ones). If trauma-related problems persist, such as intrusive memories or thoughts, trauma focused methods such as Eye Movement Desensitization and Reprocessing (EMDR) [38] and Thought Field Therapy (TFT) [39] can be applied. The family members are advised to imagine having a conversation or write to the deceased and say goodbye (eg, writing a letter to the loved one, mentioning what they did not have time to say/do; ask for forgiveness if there are any regrets) [40]. A discussion around the balance between maintaining a constructive bond with the dead and keeping the lost one too close is also addressed. In addition, an emphasis is placed on living with grief over time, principally for the next coming months (eg, resume normal activities, interact with the environment, organize/tidying the dead person’s belongings, set goals for the family, use self-help techniques with videos found on the Internet). Finally, parents receive information for learning more about children’s reactions [41].

#### Session 4

Session 4 takes place within 3 to 6 months post loss. This session starts with a discussion on what has happened since the last meeting in order to: identify what is presently regarded as most important for the family and/or the individual family members; and reinforce the acquisition of new skills and the changes that were made as a family. A special emphasis is placed on living with grief over time and recovering daily functioning, particularly in the social and work/school spheres of life (eg, family interaction, be part of and sustain a helpful social network, etc). Additionally, if the dead continues to be kept very close (ie, nothing has been changed, as if the person died the day before), some changes are encouraged such as organizing/tiding up belongings, decreasing the number of grave visits and the amount of time spent in talking or thinking about the dead, and so on. The use of the “postponed worry-technique” [42] is introduced. Specific work regarding any sleep problems is included, as well as EMDR and TFT for trauma-related problems that persist over time. Finally, this session continues to stimulate family communication and discusses how they support each other.

#### Session 5

Session 5 takes place around or following the first anniversary of the death (12-13 months after death). This session starts with a discussion on how it is to have gone through a whole year without the lost person, and how was it to pass the anniversary in order to: identify what is presently regarded as most important for the family and/or the individual family members; reinforce the acquisition of new skills and the changes that were made as a family; and prepare for the life ahead. A special emphasis is placed on living with grief over time and recovering daily functioning, particularly in the social and work spheres of life. Finally, it is discussed how family members can give themselves permission to grieve less.

The rationale for both immediate-SEIB and delayed-SEIB versions relies on the need to minimize the initial misconceptions and maladaptive appraisals that may emerge in the aftermath of a traumatic event and that may exacerbate the onset of posttraumatic symptoms and complicated grief [27]. As a result, both immediate-SEIB and delayed-SEIB seek to enhance more appropriate coping responses that are expected to have an increasing effect over time. Also, early intervention may foster an open family climate that help the family to share facts and make decisions (eg, participating in rituals, school/work reentrance), favorable for them in a long-term perspective [27]. Traumatized parents tend to shield their children from facts, thus it seems important to stimulate proper levels of family communication, emotional expressiveness, and cohesion within the first weeks after a crisis event. This may decrease the individual and family arousal, increase family resilience, and stimulate a safer environment for trauma recovery [26]. These arguments constitute the base for our immediate-SEIB intervention and are in line with our clinical and research experience, showing bereaved people ask for immediate assistance [22,29]. The immediate-SEIB first follow-up period (session 4) is consistent with the International Classification of Diseases, suggesting that complicated grief meets its diagnostic criteria when the symptoms persist beyond 6 months after the death [43]. The immediate-SEIB second follow-up period (session 5) is consistent with the Diagnostic and Statistical Manual of Mental Disorders, requiring a minimum of 12 months [44].

The delayed-SEIB proposal is informed by the literature, given most preventive studies tend to start intervention within 2 to 6 months post loss [31,32]. For the delayed-SEIB intervention group, the first 3 sessions contain less advice on the acute handling of the situation (including children in rituals, return to work and school, securing social support) and less focus on reducing bodily activation by calming family members. They prioritize the traumatic aspects surrounding the death, and psychoeducation is adjusted to the reactions usually seen at this time-point (~3 months following the loss), when the unreality has abated and the social network is often less active in their support.

Four psychologists will be responsible for SEIB delivery. They have extensive clinical experience with grief, bereavement, and trauma, and are familiar with the theoretical and empirical background that lies beneath the development of SEIB. A SEIB manual was developed and reviewed together with the psychologists. The intervention protocol is described in session-by-session detail in order to maintain treatment fidelity. The psychologists will meet with the project leader and the manual developer (first and final author) during program implementation to secure supervision and adherence to the SEIB protocol. Session-by-session, short, semistructured logs in which the psychologists and family members note their own impressions about the intervention process will also be used and discussed in the supervision contacts.

